## Abstract

**Background:**

Threatened preterm delivery (TPD) is the leading cause of inpatient admissions during pregnancy. The ability to predict the risk of imminent preterm delivery is thus a major priority in obstetrics. The aim of our study is to assess the diagnostic performance of the test to detect the placental alpha microglobulin 1 (PAMG-1) for the prediction of delivery within 7 days in women with TPD.

**Methods:**

This is a prospective multicenter diagnostic study. Inclusion criteria are singleton pregnancy, gestational age between 24 + 0 and 33 + 6 weeks inclusive, cervical measurement 25 mm or less assessed by transvaginal ultrasound (with or without uterine contractions), clinically intact membranes and cervical dilatation < 3 cm assessed by digital examination.

According to the current protocol, when a women presents with TPD and the diagnosis is confirmed by transvaginal ultrasound, a vaginal sample to test for genital infection is performed. At the same time, the midwife will perform the PartoSure® test. To perform this analysis, a sample of cervicovaginal secretions is taken with the vaginal swab furnished in the test kit.

The primary outcome is the specificity of the PartoSure® test of women who gave birth more than 7 days after their hospitalization for TPD. The secondary outcomes are the sensitivity, PPV, and NPV of the Partosure® test and the factors associated with false positives (with a univariate logistic regression model).

Starting with the hypothesis of an anticipated specificity of 89%, if we want to estimate this specificity with a confidence interval of ± 5%, we will require 151 women who do not give birth within 7 days. We therefore decided to include 400 women over a period of two years to have a larger number of events (deliveries within 7 days).

**Discussion:**

The different tests already used such as fetal fibronectin and phIGFBP-1, are not sufficiently relevant to recommend their use in daily practice. The different studies of PAMG-1 described above thus provide support for the use of this substance, tested by PartoSure®. Nonetheless, other larger studies are necessary to validate its use in daily practice and our study could answer this question.

**Trial registration:**

NCT03401255 (January 15, 2018)

## Background

Threatened preterm delivery (TPD) is the leading cause of inpatient admissions during pregnancy [1]. It is defined by a risk of preterm delivery before 37 weeks of gestation. Its prevalence in France is estimated at 60,000 cases per year [2], which represents about 7.5% of live births[3]. It is complicated by preterm delivery in nearly 30% of cases in singleton pregnancies [4–6].

The principal complication of TPD is preterm birth, which is associated with higher rates of neonatal morbidity and mortality. In 2010, around 15 million children worldwide were born before 37 weeks of gestation, that is, around 11% of live births [1, 7]. In France, approximately 60,000 children (7.4%) are born before 37 weeks of gestation each year, half of them after spontaneous labor [1].

Preterm delivery is the leading factor associated with perinatal morbidity, responsible for neonatal complications such as acute respiratory distress syndrome and necrotizing enterocolitis [8–10]. Neonatal mortality and morbidity are closely associated with gestational age at birth and are highest for fetuses born at the earliest gestational ages [11]. The ability to predict the risk of imminent preterm delivery is thus a major priority in obstetrics.

Although there is currently few treatment options to delay childbirth in the event of a short cervix [12], the ability to discriminate women who will deliver preterm from those who will give birth at term would meet two related objectives: to enable early preventive treatment and to avoid treatment and admissions determined subsequently to be futile and which generate adverse effects, potentially excessive prescriptions of corticosteroids, and futile expenses [2].

Various biochemical markers have been proposed to improve the identification of women at risk of spontaneous preterm delivery, in the hope that their use could reduce its prevalence. Foetal fibronectin and phIGFBP-1 have both shown their effectiveness in ruling out spontaneous preterm delivery within 7 to 14 days, due to their good Negative Predictive Values (NPV), but their low Positive Predictive Values (PPV) mean that they lack precision in identifying the patients at high risk of spontaneous preterm delivery within 7 days [13–15]. For these reasons, numerous hospitals have abandoned its use in daily practice, and its use would require further comparative studies [1].

Recent studies have suggested that the detection of the placental alpha microglobulin 1 (PAMG-1) protein in vaginal secretions by the PartoSure® test among women with TPD symptoms and intact membranes may have good PPV for spontaneous preterm delivery within 7 days [16, 17].

The protein Placenta Alpha Microglobulin-1 (PAMG-1) is found in high concentrations in amniotic fluid. The PartoSure® test is an immunochromatographic test designed to detect PAMG-1 in vaginal secretions when preterm delivery is imminent [18]. This test uses monoclonal antibodies with the sensitivity to detect 4 ng/µL of PAMG-1 in vaginal secretions. This protein is released by decidual cells in the amniotic cavity throughout pregnancy. It is found in vaginal secretions in women with symptoms of labor and for whom delivery is imminent.

According to the study by Lee et al. [18], this mechanism may be explained by the protein’s transudation through the pores of the fetal membranes during uterine contractions, or by the degradation of these membranes’ extracellular matrix due to an inflammatory process during labor or an infection. The PartoSure® test is simple, fast, and noninvasive, in the form of a dipstick (reagent strip) that is read instantaneously.

The test is especially interesting given that the repetition of corticosteroid treatment is currently debated and its effect is most beneficial if delivery takes place in the 24 h to 7 days after its administration [1]. Although some studies show a beneficial effect of the repetition of cures in the first weeks of life [19], repetition of corticosteroid treatment could be responsible of an increase in insulin resistance and cardiovascular risk in adulthood, as well as obesity [20]. In addition, repeated courses of corticosteroids do not seem to have any benefit on morbidity or mortality at the age of 5 years [21]. In 2016, the French National College of Gynecologists and Obstetricians (CNGOF) mentioned the use of the PAMG-1 test, but more studies are necessary to reach a conclusion about its use [1]. Further studies appear essential to specify in more detail the value of this test in women with TPD.

The aim of our study is to assess the diagnostic performance of the test to detect PAMG-1 for the prediction of delivery within 7 days in women with TPD.

## Methods / Design

### Protocol version

The reference protocol is RC17_0247 – Etude Maposure.

The N° ID RCB is: 2017-A02715-48.

The protocol version is n°9 (20/11/2017).

### Trial design

This is a prospective multicenter diagnostic study.

This is a non-interventional study. There was therefore no written consent necessary but a recipe for no opposition.

### Participating centers

The two participating centers are the Nantes University Hospital Center (UHC) (Nantes, France) and the Vendée District Hospital Center (La Roche sur Yon, France).

### Eligibility criteria

Patients are recruited from among the pregnant women receiving prenatal care in both centers.

#### Inclusion criteria

Adult woman (at least 18 year old), legally competent.provides oral consent after information.singleton pregnancy.affiliated with the French CNAMTS (salaried workers’ health insurance).gestational age between 24^+ 0^ and 33^+ 6^ weeks inclusive.cervical measurement ≤ 25 mm assessed by transvaginal ultrasound, with or without uterine contractions.clinically intact membranes.cervical dilatation < 3 cm assessed by digital examination.

The threshold of 25 mm for cervical measurement would be relevant to rule out the risk of spontaneous premature delivery at 48 h and 7 days [1]. It seems essential to us not to miss a patient who risks giving birth in the hours or days to come, taking into account the consequences of a premature child who has not received corticosteroid therapy. We therefore include more patients than if we took the 15 or 20 mm threshold (ultrasound plays the role of sensitivity) [22], hence the interest of a specific test.

#### Exclusion criteria

presence of vaginal bleeding.history of cervical conization.history of uterine malformation (bicornuate bicervical uterus, bicornuate unicervical uterus, unicornuate uterus, septate uterus).presence of polyhydramnios with amniotic fluid index > 25.obvious premature rupture of the membranes.clinical or laboratory-confirmed chorioamnionitis.cervical cerclage.intercurrent obstetric disease that might induce preterm birth.patient hospitalized for more than 24 h in another hospital or department for TPD.

We excluded patients who had a conization because the cervix is automatically shorter physiologically [23]. The 25 mm threshold cannot then apply and it remains dependent on the presence or not of uterine contractions [24]. However, these patients, like twin pregnancies, are at greater risk of prematurity, and a specific assessment would be necessary.

### Materials

To perform the PartoSure® test, a sample of cervicovaginal secretions is taken with the vaginal swab furnished in the test kit. After removing the swab from its packaging, it is held in the middle of the stem, and its extremity is carefully and gently introduced into the vagina for a length of 5–7 cm (a speculum is not necessary to take this sample), when the woman is in a supine position. The swab should be withdrawn from the vagina after 30 s. Once it has been withdrawn, the swab end containing the sample should be immediately placed into the vial of solvent furnished for this purpose, then rinsed by being rotated several times for 30 s. The swab should then be withdrawn from the vial and discarded as biomedical waste. After the dipstick is removed from its packaging, its white portion (indicated by arrows pointed downward) is inserted into the vial of solvent. The dipstick should be removed from the vial once two bands are clearly visible in the test zone, or after 5 min. Then the results are read on a clean, dry, flat surface. Two bands in the test zone indicate a positive result, while a line in the test zone indicates a negative result. It is not recommended that the results be read or interpreted after the dipstick has been immersed in the vial for more than 10 min. It is important to know that the intensity of the bands can vary. The test is considered positive even if the bands are light-colored or appear shadowed. A result is negative when only the control line appears. A test is considered invalid when the control line is absent.

This test can be used after a vaginal examination, and no special equipment or training is necessary.

It can be used between 20^+ 0^ and 36^+ 6^ weeks of gestation.

According to the current protocol, when a women presents with TPD and the diagnosis is confirmed by transvaginal ultrasound (with a cervical measurement ≤ 25 mm), a work-up to test for infection is performed, comprising a blood sample with a complete blood count (CBC), C-reactive protein (CRP), a urinary reagent strip, and a vaginal sample to test for genital infection. At the same time, the midwife will perform the PartoSure® test. The test will then be discarded, and the result reported in the CRF. Because this vaginal sample is taken at the same time as that for bacteriological testing, there is no additional gynecologic examination and no psychological risk for the woman. This research is therefore classified as noninterventional.

Cardiotocography is performed to verify fetal status and to show uterine contractions.

In case of uterine contractions, if tocolysis was necessary, the patient received either nifedipine (oral administration) or atosiban (intravenous administration), for a maximum of 48 h. Prenatal corticosteroid treatment aimed at fetal pulmonary maturation was performed with betamethasone 12 mg intramuscularly once a day for 2 days.

### Outcome measures

#### Primary outcome

The specificity of the PartoSure® test will be estimated with its 95% confidence interval. It will be defined as the number of women with a negative test divided by the number of women who gave birth more than 7 days after their hospitalization for TPD.

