#### Secondary outcomes

- The sensitivity, PPV, and NPV of the Partosure® test for the prediction of delivery within 7 days will be estimated with their 95% confidence intervals.

Sensitivity will be calculated by dividing the number of women who gave birth within 7 days and tested positive (true positives) among all the women who gave birth within 7 days.

The negative predictive value will be calculated by dividing the number of women who did not give birth within 7 days and tested negative (true negatives) by all the women who tested negative. The positive predictive value will be calculated by dividing the number of women who gave birth within 7 days and tested positive (true positives) among all the women who tested positive.

The same estimates will be performed for the diagnostic capacity of the Partosure® test for predicting delivery within 48 h.If the number of individuals allows, the same analyses will be performed according to subgroups for cervical length and gestational age at inclusion.The factors associated with false positives will be sought from a univariate logistic regression model. All of the variables significant with a P-value < 0.20 will be introduced into a multivariate model. A backward stepwise procedure will be used to determine the factors associated with a P value < 0.05, which will be retained in the final model.Costs will be presented as means with their 95% confidence intervals.

A univariate sensitivity analysis will be performed and will consider the variables of interest identified during the study, such as the cost of the PartoSure® test.

From an economic point of view, women hospitalized in the Homogeneous Patient Group 14Z16Z = False labor and threatened preterm delivery are charged a flat fee of €1,082.06 when she is hospitalized for 1 to 4 days, to which is added a daily charge of €359.21 after the 4th day. These charges must make it possible to cover all healthcare utilization (drugs, medical devices, imaging) generated by the woman during her hospitalization but also the time spent by hospital staff and the hospital’s logistics and general management.

A national accounting database estimated that the mean cost of the management described above was €2,020 in 2015. The Nantes UHC estimated this mean cost in 2016 at €2,592.15. For the women hospitalized at the District Hospital Center of La Roche sur Yon, the estimated cost was €654.26 per day of hospitalization.

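### The primary 7-day window runs from hospitalization rather than from the PAMG-1 swab, and the other 7-day and 48-h measures have no stated start; the effect on 7-day specificity is small, but the 48-h analysis is exposed

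*Protocol article*

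**What the plan says.** The Background section of the Protocol article gives the aim as the performance of the PAMG-1 test in predicting delivery within 7 days. Four places bear on when those 7 days begin.

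- **Primary outcome.** The denominator of specificity is the "number of women who gave birth more than 7 days after their hospitalization for TPD". The Abstract repeats this anchor.
- **Secondary outcomes.** Sensitivity, PPV and NPV "for the prediction of delivery within 7 days will be estimated with their 95% confidence intervals", with no starting point. A further sentence adds: "The same estimates will be performed for the diagnostic capacity of the Partosure® test for predicting delivery within 48 h". That window has no stated start either.
- **Materials.** The infection work-up follows presentation and ultrasound confirmation, and the swab belongs to it: "At the same time, the midwife will perform the PartoSure® test".
- **Exclusion criteria.** The relevant exclusion is a "patient hospitalized for more than 24 h in another hospital or department for TPD". A woman with a prior stay of 24 h or less elsewhere can therefore be enrolled and swabbed afterwards. The cost paragraphs under Secondary outcomes price in utero transfers between hospitals, so transfers are foreseen.

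The article does not say whether, for a transferred woman, hospitalization means the first admission or the admission to the study center.

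**The concern.** A prediction window should open when the predictor is measured. If it opens earlier, the time between admission and swab is event-free by construction, because a woman who delivers before the swab is never tested. The window left after the test is shortened by the same amount. A 24-h lag takes one seventh of a 7-day window and half of a 48-h window.

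The women affected are those who deliver after the window from admission has closed but before the window from the swab has closed. They are events for the question asked and non-events under the rule as written. If such a woman tested positive, a correct prediction is recorded as a false positive, which lowers specificity and PPV. If she tested negative, a missed event is recorded as a true negative, which flatters NPV. The error falls only on women with a prior stay, so it could also produce a spurious link between transfer and false positivity in the planned regression on false positives.

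With no origin stated for the secondary measures, two analysts could classify the same woman differently, or specificity and sensitivity could rest on different clocks.

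**Working it through.** **The plan's own figures (Sample size).** Specificity 89% ± 5 points: n = 1.96² × 0.89 × 0.11 / 0.05² = 150.4, so 151 women without the event. With 10% prevalence, 151 / 0.90 = 167.8, so 168. Sensitivity 75% with 17 events: 1.96 × √(0.75 × 0.25 / 17) = 0.206, stated as ± 20%. All three reproduce, and none depends on the time origin.

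**Inputs from the article.** N = 400; 10% delivering within 7 days; sensitivity 75%; specificity 89%; longest eligible prior stay elsewhere 24 h.

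**Assumptions, not in the article.** A constant delivery hazard after the swab; hospitalization read as the earlier admission; a share f of women swabbed a full 24 h after it, with f = 10%, 25% or 50%; the same sensitivity in women who deliver in the gap as in other events; and, for the 48-h rows, the same origin.

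**Share of events lost in a lagged woman.** The hazard is h = −ln(0.90)/7 = 0.01505 per day and F(t) = 1 − exp(−ht).

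- 7 days: F(7) = 0.1000 and F(6) = 0.0864, so 1 − F(6)/F(7) = 13.6%.
- 48 h: F(2) = 0.0297 and F(1) = 0.0149, so 1 − F(1)/F(2) = 49.6%.

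**Expected events among 400.** 40 at 7 days; 400 × 0.02966 = 11.9 at 48 h.

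**Women reclassified.** m = 400 × f × [F(W) − F(W − 1)], where W is the window in days. Apparent 7-day specificity is (360 × 0.89 + m × 0.25) / (360 + m).

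| f | m at 7 days | % of 40 events | Apparent 7-day specificity | m at 48 h | % of 11.9 events |
|---|---|---|---|---|---|
| 10% | 0.5 | 1.4% | 88.9% | 0.6 | 5% |
| 25% | 1.4 | 3.4% | 88.8% | 1.5 | 12% |
| 50% | 2.7 | 6.8% | 88.5% | 2.9 | 25% |
| 100% (extreme) | 5.5 | 13.6% | 88.0% | 5.9 | 50% |

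**Against precision.** With 360 non-events the half-width for specificity is 1.96 × √(0.89 × 0.11 / 360) = 3.2 points. The shift for f = 10–50% is about 0.1–0.5 points.

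**PPV at 7 days.** True positives 0.75 × 40 = 30; false positives 0.11 × 360 = 39.6; PPV = 30/69.6 = 43.1%. Moving 0.75m women from true to false positive gives (30 − 0.41)/69.6 = 42.5% at f = 10% and (30 − 2.05)/69.6 = 40.2% at f = 50%.

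**Sensitivity at 48 h.** With 9 of 12 events detected (75%), losing one event gives 8/11 = 73% or 9/11 = 82%. The direction depends on which woman is lost.

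**Other inputs.** The Discussion says 80% of women selected by cervical ultrasound do not deliver within 7 days. At 20% prevalence the specificity shift for f = 10–50% is about 0.2–1.0 points, and the 48-h share is again about 5–25% (of 24.7 events). With a 12-h lag and 10% prevalence, f = 50% gives 88.8% specificity at 7 days and about 12% of 48-h events.

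**The case against.** The strongest reply is that the Materials section ties the swab to presentation and diagnosis. For a woman who comes directly, admission and swab are nearly simultaneous and the choice of origin hardly matters. For a transferred woman the exclusion criterion limits the lag to 24 h. If hospitalization means admission to the study center, the lag is close to zero even for her. The constant-hazard model also overstates the losses if delivery risk falls after presentation. All of this stands, and it is why the effect on the primary outcome is small.

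Several stronger readings are tempting and are not supported.

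- *Everyone tested after a prior stay is misclassified.* Only women who deliver in the gap between the two window ends are, and only if the earlier admission starts the clock.
- *There is no limit on a prior stay in the recruiting department, so gaps could be long.* The exclusion does speak only of a stay "in another hospital or department for TPD", but a long stay for TPD in the recruiting unit before the swab would depart from the procedure in Materials. An earlier stay for another reason does not start a clock that runs from hospitalization for TPD.
- *Women managed as outpatients have no time zero.* The inclusion criteria do not list admission, but the article describes no outpatient management of enrolled women and bases recruitment on women hospitalized for TPD.
- *The 48-h window starts at admission.* That is an inference from the reference to the same estimates. The text can equally be read as running from the test.

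It can also be said that a full protocol may settle the secondary origins. That does not answer the primary outcome, where the article states an origin and it is not the swab.

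**Conclusion.** The point holds in a limited form. The primary outcome is anchored to admission although the question concerns the test, and the article's eligibility rule allows the two to differ by up to 24 h. For 7-day specificity the consequence is minor: about 0.1–0.5 points at 10% prevalence, against a half-width of about ± 3.2. The main exposure is the 48-h analysis, where 5–25% of roughly 12 expected events would be reclassified if it uses the same origin. The search for factors behind false positives is exposed to the same error.

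These are ranges and not estimates. They rest on an assumed 10–50% of women lagging a full 24 h, a constant hazard, and the earlier admission being taken as time zero. The article gives no figure for the share of women with a prior stay. The sample size is not in question.

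**What to change.** Define every 7-day and 48-h outcome as the time from the date and time of the PartoSure swab to the date and time of delivery. Use that origin for specificity, sensitivity, PPV, NPV, their subgroup versions and the definition of a false positive in the regression. The Primary outcome definition and its repetition in the Abstract would change, and one sentence under Secondary outcomes would state the origin.

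The cost is small. The swab date and time must be recorded in the CRF; the article mentions only that the test result is entered there. Since the swab is taken together with the bacteriology sample, that sample's collection time could stand in where the swab time is missing, provided it is recorded, which the article does not say. The figures of 151, 168 and 400 are unaffected.
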